### Safety outcomes

Participants will undergo laboratory tests at baseline and week 4, including liver and kidney function (ALT, AST, Scr, BUN), blood routine test, urine routine test, and stool routine test. Other tests include an electrocardiograph examination.

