## Methods/design

### Study design and setting {8-9}

This is a single-center, double-blinded, placebo-controlled, randomized controlled trial (RCT), which will be conducted in Dongfang Hospital, Beijing University of Chinese Medicine. The study is conducted in accordance with the Declaration of Helsinki (Edinburgh 2000 version). The final protocol (Version 2.0, 11 November 2020) of this trial has been approved by Ethical Committee of Dongfang Hospital, Beijing University of Chinese Medicine (Version number: JDF-IRB-2020033602). In addition, this trial has been registered in the Chinese Clinical Trial Registry (No. ChiCTR2000041225, registered on 22 December 2020).

We aim to enroll 72 patients with NERD over a 2-year period (Date from November 2020 to December 2022) from the department of gastroenterology in Dongfang Hospital, Beijing University of Chinese Medicine. Eligible patients will be randomized at a ratio of 1:1 to either TCM group (HWJNR with omeprazole enteric-coated tablets placebo) or western medicine group (omeprazole enteric-coated tablets with HWJNR placebo) for 8 weeks treatment. At the end of this trial, the primary outcome (GERD-Q) and the secondary outcome (SF-36, PRO, syndrome score of TCM) will be evaluated. We will obtain peripheral venous blood, urine, and stool from NERD patients before and after treatment. This study involves 3 site visits (week 0, week 4, and week 8) and 10 call visits (weekly call during the treatment period and follow-up at month 1 and month 3). The process of the study is schematically shown in Fig. 1. And we will additionally recruit 10 healthy controls.

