### Interventions {11}

#### Intervention description {11a}

TCM group was given HWJNR with omeprazole enteric-coated tablets placebo; western medicine group was given omeprazole enteric-coated tablets with HWJNR placebo. The course of treatment is set for 8 weeks. Medication method and dose were as follows: omeprazole enteric-coated tablets/placebo: 20 mg, once a day, half an hour before breakfast; HWJNR/placebo: twice a day, one bag at a time, half an hour after breakfast and dinner. For production of formula placebo: the TCM placebo is made by Beijing Kangrentang Pharmaceutical Co., Ltd., according to the preparation process of HWJNR. The shape, color, gas, and taste will be similar to HWJNR after adding the same kind and equal amount of excipients. Finally, 5% of the original unit treatment drug is added to correct color and taste.

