### Biological specimens {26b,33}

We will collect human samples including blood, urine, and feces. These samples will be used for blood routine test, urine routine test, stool routine test, and liver and kidney function test. The feces will additionally be used to detect the relationship between fecal flora and metabolites. All specimens will be destroyed after examinations.

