Before the trial, no AE has been reported in the clinical application of HWJNR. The possible AEs of omeprazole enteric-coated tablets include diarrhea, headache, nausea, abdominal pain, flatulence and constipation, and occasional increase of serum aminotransferase (ALT, AST), rash, dizziness, and so on. These AEs are usually mild and can disappear automatically, which have nothing to do with the dose. Since the omeprazole enteric-coated tablets used in this study belong to the routine treatment of NERD, these AEs may also occur even if the subjects do not participate in the clinical study. During the study, we will closely monitor AEs and take measures to prevent them. Once the emergencies related to the study occur, the research assistant will record the detailed information including symptoms, signs, severity, start date, duration, lab results, intervention, and the results of adverse events at each visit. And the subjects will have the right to receive corresponding compensation.

Serious adverse event (SAE) refers to any adverse medical accident that occurs at any dose, including death, life-threatening conditions, the need for hospitalization or prolongation of existing hospitalization, persistent or significant disability/incapacity, or congenital anomaly/birth defect. Once SAEs occur, the events must be reported to the principal investigator and the Ethics Committee and the Beijing Food and Drug Administration within 24 h. The principal investigator has the power to terminate the trial if necessary.

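### Safety laboratory tests are listed at baseline and week 4 of an 8-week treatment, while other sections imply an end-of-treatment panel

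*Protocol article*

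**What the plan says.** Safety outcomes fixes the times of the laboratory panel: "Participants will undergo laboratory tests at baseline and week 4". The panel covers ALT, AST, Scr and BUN, with routine blood, urine and stool tests. Under Intervention description, "The course of treatment is set for 8 weeks".

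Study design and setting describes the sampling differently: "We will obtain peripheral venous blood, urine, and stool from NERD patients before and after treatment". It also places site visits at weeks 0, 4 and 8. The contacts at months 1 and 3 are telephone calls.

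Biological specimens says what the blood, urine and feces are for: "These samples will be used for blood routine test, urine routine test, stool routine test, and liver and kidney function test". It adds one further use, for one specimen type only: "The feces will additionally be used to detect the relationship between fecal flora and metabolites". It gives no time points.

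**The concern.** The list in Safety outcomes stops halfway through treatment, yet blood and urine are also to be taken after treatment and have no stated purpose except the safety panel. Either an end-of-treatment panel is intended and Safety outcomes is incomplete, or week 4 really is the last panel.

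In the second case, a symptomless liver, kidney or blood abnormality arising in weeks 5 to 8 would not be picked up by any scheduled test, and a laboratory safety conclusion for the full course would lack data. Safety is a stated aim of the trial. The section on adverse events itself names occasional aminotransferase rises with omeprazole. For the herbal recipe it relies on no adverse event having been reported in earlier clinical use, so laboratory data at the end of treatment would be informative for both arms.

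**Working it through.** **Comparing the sections.**

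| Section | Baseline | Week 4 | After treatment (week 8) |
|---|---|---|---|
| Safety outcomes (laboratory panel) | yes | yes | not listed |
| Study design and setting (blood, urine, stool) | yes | not mentioned | yes |
| Biological specimens (uses of samples) | no times given | no times given | no times given |

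The first two rows agree only on baseline. Reading the second row as a safety panel is an inference: it joins the sampling times in one section to the uses in another. The support for it is that feces have a second, mechanistic use, which could explain a post-treatment stool sample, but blood and urine have none. Elsewhere the article names week 8 when it means it. GERD-Q, SF-36, the PRO scale and the TCM syndrome score are at baseline, week 4 and week 8, and the mechanistic outcome is at baseline and week 8.

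**Uncovered time if Safety outcomes is complete.** 8 − 4 = 4 weeks, and 4/8 = 50% of the treatment period.

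**Effect on detection.** The plan gives no figure to reproduce and no event rate. The following are assumptions:
- a constant weekly hazard;
- an abnormality that persists until it is sampled;
- 8-week cumulative incidences p8 of 2%, 5% and 10%.

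Group sizes come from the Sample size section: 36 recruited per group, and the 30 calculated before the dropout allowance.

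Incidence by week 4: p4 = 1 − (1 − p8)^0.5. Chance of at least one case in a group of n: 1 − (1 − p)^n, with p = p8 if the last panel is at week 8 and p = p4 if it is at week 4.

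For example, with p8 = 0.05, p4 = 1 − 0.95^0.5 = 0.0253. With n = 36, the chance is 1 − 0.95^36 = 0.842 at week 8, against 1 − 0.95^18 = 0.603 at week 4.

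| p8 | p4 | n = 36, week 8 | n = 36, week 4 | n = 30, week 8 | n = 30, week 4 |
|---|---|---|---|---|---|
| 2% | 1.01% | 0.517 | 0.305 | 0.455 | 0.261 |
| 5% | 2.53% | 0.842 | 0.603 | 0.785 | 0.537 |
| 10% | 5.13% | 0.977 | 0.850 | 0.958 | 0.794 |

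The loss is larger if the hazard rises with cumulative exposure and smaller if abnormalities arise mainly early. If they resolve on their own before sampling, the chances in both schedules are lower than shown.

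**The case against.** The strongest reply is that the deciding source cannot be seen. Table 4 is the assessment schedule and may well list a week-8 panel. Nor do the sentences strictly collide: Safety outcomes does not say that its two time points are the only ones, and the sampling statement in Study design and setting is a general overview. On that view Safety outcomes is merely abbreviated, and the harm arises only on the reading that the other sections argue against. This stands in part. It cannot be said that the full schedule omits week 8, and the gap in weeks 5 to 8 is conditional. But Safety outcomes states definite time points. If Table 4 does list week 8, that section disagrees with it and still needs correcting.

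A second reply is that weeks 5 to 8 are not unmonitored. There are weekly calls, a week-8 site visit, adverse event recording at each visit, re-examination of out-of-range results and a Data and Safety Monitoring Committee. All of this is true and limits the clinical stakes. None of it detects a symptomless abnormality when no sample is scheduled.

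A third reply is that the detection figures rest on assumed incidences and on persistence, while the protocol describes the listed omeprazole events, raised ALT and AST among them, as usually mild and self-resolving. That is fair. The figures show the possible size of the loss and are not estimates for this trial. The only figure that comes from the document itself is 4 of 8 weeks.

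**Conclusion.** The concern holds: the text gives two schedules for the safety laboratory tests. Following Safety outcomes as written leaves 4 of 8 treatment weeks with no later scheduled test. With 36 patients per group, the chance of seeing at least one case in a group would then fall from 52% to 31%, from 84% to 60%, or from 98% to 85%, for assumed 8-week incidences of 2%, 5% and 10%. Following the other two sections, the loss is zero and the defect is one of wording. Which reading is meant cannot be settled without Table 4, so confidence in an actual safety gap is moderate. The need to correct the text does not depend on the answer.

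**What to change.** State in Safety outcomes that the full panel is done at baseline, week 4 and week 8. Say in Study design and setting that blood and urine are also taken at week 4, add the time points to Biological specimens, and check that Table 4 matches. If no week-8 panel is to be done, limit the laboratory safety conclusion to the first 4 weeks of treatment and say what the post-treatment blood and urine are for.

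If the after-treatment samples are already meant for the safety panel, this is an edit to the text only. Otherwise it adds at most one routine panel per patient, at a site visit that is already planned.

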### Participant timeline {13}

Table 4 shows the schedule of enrollment, treatment, and assessment.

**Table 4 Tab4:**
[figure not shown]
Schedule of enrollment, treatment, and assessment

*The mechanistic outcome will be analyzed in experimental group (TCM group and western medicine group) at the baseline and week 8, and in normal subjects at baseline

### Biological specimens {26b,33}

We will collect human samples including blood, urine, and feces. These samples will be used for blood routine test, urine routine test, stool routine test, and liver and kidney function test. The feces will additionally be used to detect the relationship between fecal flora and metabolites. All specimens will be destroyed after examinations.

#### Data collection and management {18,19}

##### Recording requirements of the CRFs

All records will be collected and screened by investigators, who has been trained and qualified. Researchers must fill in the research forms in a timely, accurate, complete, and standardized manner based on the relevant regulations and instructions. All data will be collected, including the participant retention and complete follow-up. If there is any doubt about the data, our investigator will send an “electronic data inquiry” to the researcher. The researcher should reply as soon as possible. The main researchers will be responsible for the authenticity of the research data.The laboratory test must be pasted on the “Research Medical record.” The laboratory test or description recorded in the CRFs should be checked correctly with the original test report. Once the CRFs are complete, the original record will not be changed, even if any modifications are made. The completed CRFs will be reviewed by a clinical inspector.The data of laboratory examination items outside the normal range should be confirmed by the researchers and reexamined. During the course of the trial, abnormal examination items with clinical significance should be recorded and followed up based on adverse events.All data will be kept by a special person.

##### Selection of dataset

Full analysis set (FAS): FAS refers to the intention-to-treat (ITT) analysis of all patients who have been randomized into groups and assigned to random numbers (called willing treatment groups). Errors that do not meet the inclusion criteria or exclusion criteria are excluded.Per-protocol set (PPS): PPS refers to the statistical analysis of all cases that is in accordance with the clinical observation plan (Compliance with medication ranging from 80 to 120% will be eligible for the protocol analysis set). Subjects will not take prohibited drugs during the observation period, and completed the CRF requirements.Safety set (SS): Safety data should include all subjects who have received at least one treatment and at least one safety assessment after randomization.

### Statistical analysis {20}

Efficacy analysis will be performed based on both FAS and PPS patients. Safety analysis includes all randomized participants who take at least one bag of HWJNR and have data for safety assessment. Comparing the healthy control group with the traditional Chinese medicine group, we will study the composition of the intestinal flora and the expression of metabolites in patients with NERD and the healthy group. And it will also reveal the mechanism of action and advantages of HWJNR in the treatment of NERD patients.

Changes from baseline to post-treatment in GERD-Q, SF-36, PRO, and syndrome score of TCM will be analyzed using analysis of covariance with associated 95% confidence intervals. All the analysis results will be generated by SPSS 25.0 software. Repeated measurement data are expressed by mean ± standard deviation, intra-group comparison is performed by analysis of variance of repeated measurement data, and inter-group comparison is by multivariate analysis of variance (MANOVA). *P* ≤ 0.05 indicates that the difference is statistically significant. Unilateral test will be used in all statistical tests, and the significance level *P* ≤ 0.05. The arithmetic mean, standard deviation, median, minimum, and maximum will be calculated according to the data distribution. Counting data will be used to calculate the number and percentage of cases.

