(4)Mechanistic outcome: The samples will be used to study the composition structure and metabolite expression profile of intestinal flora in NERD patients through 16s rRNA sequencing and metabonomic association analysis in TCM group, western medicine group at baseline and week 8, and in normal subjects at baseline. By analyzing the correlation between a variety of differential flora and differential metabolites, we will demonstrate the effects of changes in the structure of intestinal flora on metabolic phenotypes and functional metabolic small molecules. This experiment attempts to screen some key strains through visual tools, further explore their mechanism in the pathogenesis of NERD, identify the advantages of treatment, and reveal the potential mechanism of HWJNR. The determination of intestinal flora and metabolites will be performed by Shanghai OE Biotech Co., Ltd (Shanghai, China).(5)Follow-up recurrence index: The number and percentage of the subjects with non-medication, maintenance medication, intermittent medication, and on-demand medication will be recorded at month 1 and month 3 respectively.

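### The statistics section rests claims about HWJNR's mechanism and advantages on healthy controls versus the TCM group, leaving out the randomised western medicine arm that the outcome definition includes

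*Protocol article*

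**What the plan says.** Three places in the protocol article describe the mechanistic analysis.

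- **Statistical analysis {20}** names one comparison for flora and metabolites: "Comparing the healthy control group with the traditional Chinese medicine group, we will study the composition of the intestinal flora". The next sentence adds the inference: "And it will also reveal the mechanism of action and advantages of HWJNR in the treatment of NERD patients". The analysis of covariance described in the following paragraph is for GERD-Q, SF-36, PRO and the TCM syndrome score. It does not mention flora or metabolites.
- **Secondary outcome measurements, item (4)** defines the outcome as sequencing and "metabonomic association analysis in TCM group, western medicine group at baseline and week 8, and in normal subjects at baseline". On selecting strains it says: "This experiment attempts to screen some key strains through visual tools".
- **The Table 4 footnote** says: "The mechanistic outcome will be analyzed in experimental group (TCM group and western medicine group) at the baseline and week 8", with normal subjects at baseline.

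Statistical analysis {20} also sets a general rule, "Unilateral test will be used in all statistical tests", at P ≤ 0.05, whereas Sample size {14} uses a two-sided type I error of 0.05. Ten healthy controls and 36 patients per arm are planned.

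**The concern.** Explaining how HWJNR works is a stated aim in the Abstract and the Introduction. A statement that HWJNR changed the flora, or did so to better effect than omeprazole, is causal and comparative. In this trial only the randomised comparison of the two arms supports such a statement, and the statistics section does not name that comparison for flora or metabolites. An analyst working from that section alone could report a confounded contrast as the mechanism of HWJNR and leave the randomised contrast, available from the same planned samples, in the background.

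The blanket one-sided rule also suits this outcome poorly. Taxa and metabolites can rise or fall, and a one-sided test in a preset direction cannot detect a change in the other.

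**Working it through.** **1. The plan's own figure.** No calculation is given for the mechanistic outcome. The only computed figure, in Sample size {14}, reproduces: 2 × 0.766 × 0.234 × 2.8² / 0.308² = 29.63, rounded up to 30 per group. It sizes a clinical effective rate with two-sided alpha 0.05. It bears on this point only because it shows which sidedness the design used.

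**2. What each contrast can show.** Statistical analysis {20} does not say at which visit the TCM group is compared with the healthy controls, so both readings are set out, along with the alternatives.

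| Contrast | Randomised? | What the difference contains |
|---|---|---|
| Healthy (baseline) vs TCM (baseline) | No | Disease and other differences between the groups; nothing about HWJNR, which has not yet been given |
| Healthy (baseline) vs TCM (week 8) | No | Disease, 8 weeks of elapsed time, HWJNR, and symptom relief by other means |
| TCM week 8 vs TCM baseline | No | HWJNR, elapsed time, and symptom relief by other means |
| TCM vs western medicine at week 8, adjusted for baseline | Yes | The difference between assigned treatments |

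The healthy controls are sampled once, so they give no information on change over 8 weeks. Symptom relief by other means is possible because Adverse reaction {11b} allows hydrotalcite in both groups. The groups may also differ in recent medication: patients must have been free of PPIs, H2 antagonists and mucosal protectants for 2 weeks, and the listed healthy-subject criteria set no such condition. Any statement about advantages needs a comparator treatment, which the named comparison lacks.

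**3. Precision of the disease contrast.** In SD units the standard error is √(1/n₁ + 1/n₂).

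- TCM arm only, 36 vs 10: √(1/36 + 1/10) = 0.357
- Both arms, 72 vs 10: √(1/72 + 1/10) = 0.337
- Ratio 0.337 / 0.357 = 0.94, so about 6% smaller

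The gain is modest because the 10 controls dominate the variance.

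**4. Detectable difference.** For a single feature at two-sided 0.05 and 80% power, the detectable difference is (1.96 + 0.84) × standard error:

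- Healthy vs TCM, 10 vs 36: 1.00 SD
- TCM vs western medicine, 36 vs 36: 0.66 SD
- TCM vs western medicine, 30 vs 30 after dropout: 0.72 SD

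The randomised contrast is unconfounded and also the more sensitive of the two. Baseline adjustment is not credited in these figures.

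**5. Conditional point on multiplicity.** The article gives no feature count, so the counts here are assumed. If P ≤ 0.05 were applied to each feature without adjustment and all were null, the expected number flagged is m × 0.05: 2.5 for m = 50, 10 for m = 200, 50 for m = 1,000.

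**6. Sidedness.** With the direction fixed in advance, a one-sided test at 0.05 has the same null error as a two-sided test at 0.05. If the direction is chosen after seeing the data, the null error is 2 × 0.05 = 10%.

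**The case against.** The strongest reply is that the western medicine arm is not left out of the protocol. The outcome definition includes it at both visits, and the Table 4 footnote says it will be analysed, not merely sampled. The healthy-versus-TCM sentence has a natural purpose, describing NERD against health, and it does not say that no other comparison will be made. Much of this stands. A reader might infer that the omeprazole samples go unused or that the design cannot attribute flora changes to treatment; the documents do not support either inference. What remains is that the sentence on mechanism and advantages follows directly on this one comparison, and nothing else in the statistics section supplies the randomised contrast for these features.

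A reader might also infer that every taxon and metabolite is screened at an unadjusted one-sided 0.05, and that many false key strains must follow. That goes too far. The article nowhere says the tests are unadjusted, and a significance level of 0.05 is compatible with adjusted P values. The stated means of screening key strains is visual. Correlations are planned between features already found to differ, not across a full grid. A false discovery rule may stand in a full protocol or analysis plan that is not shown, so its absence here is no finding. Nor does a one-sided test with a preset direction raise the null error.

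Finally, the outcome is secondary and exploratory by its own wording. That limits the consequences but does not make the named comparison fit the stated conclusion.

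**Conclusion.** The point holds in limited form. The comparison named in Statistical analysis {20} cannot support the claim about HWJNR's mechanism and advantages that is attached to it, and it disagrees with the outcome definition and the Table 4 footnote over which groups are analysed. This is a fault in the stated analysis, not in the sampling design, which already provides what is needed.

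The main harm is confounding, and the documents give no basis for putting a figure on it. The measurable loss, a standard error about 6% larger than necessary for the disease contrast, is small and assumes all 72 patients and 10 controls give usable baseline samples. The multiplicity figure of about 5% of null features is conditional on unadjusted per-feature testing, which the article does not state. The conflict between one-sided tests and the two-sided design alpha is stated in the text. Primary efficacy and safety conclusions are unaffected by the mechanistic comparison.

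**What to change.** Bring Statistical analysis {20} into line with the outcome definition and the Table 4 footnote by stating:

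1. **Disease contrast:** all randomised NERD patients at baseline versus the healthy controls, described as non-randomised.
2. **Treatment contrast:** week-8 flora and metabolite features compared between the TCM and western medicine groups, adjusted for the baseline value. Any statement on HWJNR's mechanism or advantages should rest on this contrast and be worded as relative to omeprazole, because the comparator is an active treatment.
3. **Sidedness:** two-sided tests for these features, consistent with the sample size section.
4. **Multiplicity:** if features are tested individually, control the false discovery rate (for example Benjamini-Hochberg at 5% or 10%) across taxa, metabolites and their correlations, or refer to the document where this is already set.

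The cost is a change of analysis wording. All the samples are already planned, and no patients or visits are added. The downside is that fewer features will be declared significant.

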### Sample size {14}

According to clinical experience, the effective rate of NERD in the TCM group was P1 = 92.0%. The NERD effective rate of the western medicine group was P2 = 61.2% [(two-sided type I error rate of 0.05, *α* = 0.05); (one-sided type I error rate of 0.20, *β* = 0.20)]. The sample size is calculated by the following formula:
$$ n=\frac{2\overline{p}\overline{q}{\left({Z}_{\alpha }+{Z}_{\beta}\right)}^2}{{\left(P1-P2\right)}^2} $$

*n*1 = *n*2 = 2 × 0.766 × 0.234 × 2.8^2^ ÷ 0.308^2^ = 30. Taking approximate dropouts of 20% into account, the number of participants recruited was estimated to be 36 per group. Therefore, a total of 72 patients will be recruited in this trial. And we will additionally recruit 10 healthy controls.

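### Unless missing scores are imputed first, the ANOVA, MANOVA and ANCOVA named for efficacy use only about 80% of the ITT-type full analysis set and discard dropouts' week-4 scores

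*Protocol article*

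**What the plan says.** All statements are in the protocol article.

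- **Analysis set.** Under Selection of dataset, "FAS refers to the intention-to-treat (ITT) analysis of all patients who have been randomized into groups and assigned to random numbers". The next sentence removes ineligible patients: "Errors that do not meet the inclusion criteria or exclusion criteria are excluded". Nothing there removes patients who drop out.
- **Use of the sets.** Under Statistical analysis {20}, "Efficacy analysis will be performed based on both FAS and PPS patients".
- **Methods.** The same section says that changes in GERD-Q, SF-36, PRO and the TCM syndrome score "will be analyzed using analysis of covariance with associated 95% confidence intervals". For repeated measurements, "intra-group comparison is performed by analysis of variance of repeated measurement data, and inter-group comparison is by multivariate analysis of variance (MANOVA". The software is fixed: "All the analysis results will be generated by SPSS 25.0 software".
- **Visits.** Under Outcomes {12}, GERD-Q is scored at baseline, week 4 and week 8, and the week-8 score is the main outcome.
- **Expected loss.** Sample size {14} reaches 36 per group with this allowance: "Taking approximate dropouts of 20% into account".

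The article gives no rule for missing scores. Such a rule may stand in the full protocol or the analysis plan, so its absence here is not the point.

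**The concern.** The set and the methods do not fit together by themselves. Repeated-measures ANOVA and MANOVA in the general linear model need a complete row for each patient. ANCOVA of change at week 8 needs baseline and week 8. A patient who is seen at baseline and week 4 and then leaves belongs to the full analysis set, but enters none of these analyses unless a value is supplied for the missing visit. The result would carry an intention-to-treat label while resting on completers.

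Two things are at stake. The first is power, because week-4 scores already collected inform the week-8 mean and are not used. The second is bias. If patients doing badly at week 4 leave more often, and this happens more in one arm, the completers in that arm look better than the arm as randomised and the difference shrinks.

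**Working it through.** **Planned numbers.** Sample size {14}: 2 × 0.766 × 0.234 × 2.8² ÷ 0.308² = 29.63, so 30 per group; 30 × 1.2 = 36. Both stated figures are reproduced. They rest on response rates (92.0% against 61.2%), so they do not give the power for the GERD-Q score.

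**Patients analysed without imputation.** Take all 72 as eligible and every dropout as lacking week 8.

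- Per arm: 36 × 0.80 = 28.8. Total: 72 × 0.80 = 57.6. Lost: 72 − 57.6 = 14.4.
- If a further 5% or 10% of completers miss only week 4 (assumed; the article gives no such rate), MANOVA and repeated-measures ANOVA keep 57.6 × 0.95 = 54.7 or 57.6 × 0.90 = 51.8. ANCOVA at week 8 still keeps 57.6.
- In one simulated data set of 72, 14 had no week-8 score and half of those had week 4. MANOVA used 58 patients, ANCOVA 58, and a mixed model on weeks 4 and 8 used 65.

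**Power under random loss.** The article gives no SD or correlations. Assumed: SD 3, true week-8 difference 2, two-sided 0.05, and correlations of 0.5 (baseline–week 4), 0.4 (baseline–week 8) and 0.7 (week 4–week 8).

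- Completer ANCOVA: residual SD = 3 × √(1 − 0.4²) = 2.750; SE = 2.750 × √(2/28.8) = 0.725; 2/0.725 = 2.76; power ≈ Φ(2.76 − 1.96) = 79%.
- With dropouts' week-4 scores: the partial correlation of weeks 4 and 8 given baseline is (0.7 − 0.5 × 0.4)/√(0.75 × 0.84) = 0.63, squared 0.397. The variance factor is 1 − 0.397 × 0.20 = 0.921; SE = 0.725 × √0.921 = 0.695; power ≈ Φ(2.88 − 1.96) = 82%.
- The gain is about 3 points if every dropout has a week-4 score. If only half do, the factor is 1 − 0.397 × (1 − 57.6/64.8) = 0.956 and power is about 81%, a gain of about 2 points.
- Simulated trials with the same inputs gave 76% against 79% and 77% against 82%, with no bias. Hence 3 to 5 points.

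**Dropout driven by the week-4 score.** Same inputs, simulated; completer ANCOVA against all available data.

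| Dropout, worse v better arm | Completers: estimate, power | All data: estimate, power |
|---|---|---|
| 26% v 20% | 1.96, 74% | 2.02, 82% |
| 25% v 17% | 1.90, 73% | 2.00, 81% |
| 28% v 17% | 1.84, 70% | 2.00, 80% |
| 29% v 16% | 1.81, 69% | 2.01, 78% |
| 33% v 18% | 1.73, 64% | 1.99, 79% |
| 33% v 17% | 1.67, 62% | 2.00, 78% |

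Every row averages more than the planned 20% (for example, (25 + 17)/2 = 21% and (33 + 17)/2 = 25%), so the lower rows are upper-end cases. With total dropout held at 20%, the completer estimates were:

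- No arm difference at week 4: 1.97 to 2.02, that is, no bias at any strength of dependence.
- One-point difference at week 4: 1.95 to 1.96 at a logit slope of 0.5 to 1 per SD, and 1.87 at a slope of 2.
- About 1.8 was reached only with a week-4 difference of 1.5 to 2 points and strong dependence.

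**The case against.** The strongest reply is that patients are lost only if nothing is imputed. Naming ANCOVA or MANOVA does not prescribe a complete-case analysis, and a condensed article may leave the imputation rule to a document not shown. This stands, and the point is therefore conditional. What remains is that none of the named models uses a dropout's week-4 score by itself, so the match between set and method rests entirely on a step outside them.

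Four further objections are correct and limit the claim:

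- ANCOVA at week 8 keeps a patient who missed only week 4.
- The 20% is dropout, not a rate of missed visits.
- The full analysis set is not strictly everyone randomised, because ineligible patients are removed.
- The repeated-measures ANOVA is a within-group analysis and does not compare the arms.

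None of these returns the 14.4 patients without week 8.

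It can also be said that the bias figures depend on assumed inputs and an assumed direction. That is right: other dropout patterns could bias the other way, and under random loss there is no bias at all. Finally, the mixed model does not analyse everyone either, since a patient with no post-baseline score adds nothing to it.

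**Conclusion.** The point holds in conditional form. Without prior imputation, the named between-group methods analyse about 57.6 of 72 patients at the plan's own dropout rate and ignore week-4 data already collected on those who leave. The cost is modest: about 3 to 5 points of power under random loss, less if many dropouts lack week 4. Dilution of a 2-point effect is slight (about 1.93 to 1.96) under moderate dependence of dropout on the week-4 score with differing rates by arm. It reaches about 1.7 to 1.8 only under strong dependence. All power and bias figures rest on the assumed SD, effect and correlations.

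A reader might infer that the full analysis set cannot be analysed at all with these methods, or that any missed visit removes a patient from the primary comparison. The document supports neither reading. Imputation before analysis would keep the whole set, and the week-8 ANCOVA does not need week 4.

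The change should be made because it is cheap and uses more of the data, not because the trial would otherwise fail.

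**What to change.** Replace both the ANCOVA sentence and the ANOVA/MANOVA sentence, as between-group efficacy analyses, by one mixed model for repeated measures (SPSS MIXED, REML). Changing only the second sentence would leave a complete-case ANCOVA beside the new model.

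- Outcomes: scores at weeks 4 and 8.
- Terms: arm, visit, arm × visit, baseline and baseline × visit, with unstructured covariance.
- Patients: all in the full analysis set with any post-baseline score.
- Primary result: the week-8 difference between arms in GERD-Q with its 95% confidence interval.
- The same model for SF-36, PRO and the TCM syndrome score.
- Two statements alongside: the model assumes data missing at random, and patients with no post-baseline score contribute nothing unless imputed.

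The cost is analysis wording only. No visit, measurement, patient or software is added.
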